### Statistical analysis

A detailed statistical analysis plan will be developed and published prior to data analysis. The primary analysis will compare the intervention group to the usual care control group in terms of patient satisfaction with care, specifically focusing on the subscale affective behavior. As some patients allocated to the intervention refrain from the intervention, the statistical analysis plan will outline how such non-adherence will be accounted for using the estimand framework [39,40]. Secondary and sensitivity analyses will be specified to address alternative clinical questions and analytical scenarios.

An intermediate analysis will be performed once 40% of the total sample has been randomized. This analysis will evaluate the proportion of patients that have completed the primary outcome measurement, as well as the refusal rate in the intervention group. If the refusal rate is higher than expected (i.e., > 10%), a sample size re-estimation may be considered to increase the sample size and maintain adequate power.

Approaches to handling non-adherence will be described in the statistical analysis plan and will be aligned with the estimand. The extent and patterns of missing data will be evaluated. If appropriate, multiple imputation methods will be used to address missing data under the assumption that data is missing at random (MAR). If the primary outcome data is determined to be missing not at random (MNAR), sensitivity analyses using best–worst and worst-best case scenarios will be performed to assess the robustness of the findings.

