### Sample size

Based on internal observations (unpublished), we expect to enrol approximately 520 patients per year in PRESENT + . Currently, 79% of the patients participating in the PRESENT+ cohort provided consent to randomization into future intervention studies. Of those, approximately 40% are expected to meet the inclusion criteria for participation. Therefore, about 520 * 0.79 * 0.40 = 164 patients will be eligible every year for randomization in a 1:1 ratio to the intervention or control group. After 1.5 year of enrollment into the TIPZO-RT trial, we expect to have randomized 246 patients.

Of the patients offered a consultation with the PCCT, it is anticipated that 30% will refrain from the intervention. In a previous study, the mean score of patient satisfaction with care (interpersonal skills, EORTC IN-PATSAT32, which is most closely related to the primary outcome of this study (affective behavior, EORTC PATSAT-C33)) was 70.0 (SD = 21) among patients with metastatic solid tumors [37,38]. With a sample size of 246 patients, taking into account a refusal rate of 30% in the intervention group, 80% power, and a two-sided alpha of 0.05, the study is powered to detect a minimal difference of 7.6 points on patient satisfaction with care at four weeks follow-up (0.7 * 80.8 + 0.3 * 70.0).

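### The interim rule calls refusal above 10% higher than expected, yet the sample size is built on 30% refusal, so the condition is met when the trial runs exactly to plan

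*Protocol article*

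**What the plan says.** In the protocol article, the Sample size section states: "Of the patients offered a consultation with the PCCT, it is anticipated that 30% will refrain from the intervention". That rate enters the power statement directly, "taking into account a refusal rate of 30% in the intervention group, 80% power, and a two-sided alpha of 0.05". The diluted mean is written out as 0.7 × 80.8 + 0.3 × 70.0, with a reference score that "was 70.0 (SD = 21) among patients with metastatic solid tumors". On this basis, "the study is powered to detect a minimal difference of 7.6 points on patient satisfaction with care at four weeks follow-up".

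The Statistical analysis section plans an intermediate analysis once 40% of the total sample has been randomized. It looks at two quantities: completion of the primary outcome measurement and refusal in the intervention group. The decision rule reads: "If the refusal rate is higher than expected (i.e., > 10%), a sample size re-estimation may be considered to increase the sample size". The stated purpose of an increase is to keep adequate power.

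**The concern.** The expected refusal rate cannot be 30% in one section and 10% in the next. The quantity is the same (declining the offered consultation) and so is the arm. The article nowhere gives 10% as an expectation.

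The rule exists to detect loss of power through dilution. Read as printed, its condition is met across the whole range from 10% to 30% refusal, where dilution is no worse than the design already allows for. Two outcomes are then possible. The team may extend recruitment without need, using consultation-team capacity that the Discussion describes as limited. Or it may learn to disregard a condition that is always met, and have no working criterion if refusal really exceeds the planning value. This is the only numerical interim threshold in the article, and researchers are not blinded to allocation, so a clear rule fixed in advance matters.

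**Working it through.** **Inputs, all from the protocol article.** N = 246, 1:1, so 123 per arm; SD 21; control mean 70.0; mean in acceptors 80.8; two-sided alpha 0.05; planned refusal 30%; look at 40% randomized. As in the plan's formula, patients who decline have the control mean. No allowance is made for missing outcomes, because the Sample size section states none.

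**Step 1: reproduce the plan's figure.** The effect in acceptors is 80.8 − 70.0 = 10.8 points. With refusal r, the difference between arms is (1 − r) × 10.8. At r = 0.30 this is 0.70 × 10.8 = 7.56, printed as 7.6. With a normal approximation, 80% power for 7.56 points needs 122 per arm, or 244 in total, against the stated 246. Power at 123 per arm is 80.3% by the two-sample t-test (80.6% by the normal approximation). The stated sample size therefore rests on 30% refusal. With 10% refusal the difference would be 9.72 and the same inputs would need only 148 patients.

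**Step 2: power of 246 patients by refusal rate** (two-sample t-test, 123 per arm).

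| Refusal | Difference, (1 − r) × 10.8 | Power |
|---|---|---|
| 10% | 9.72 | 95% |
| 20% | 8.64 | 90% |
| 30% | 7.56 | 80% |
| 40% | 6.48 | 67% |
| 50% | 5.40 | 52% |

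With complete data, power drops below 80% only once refusal passes 30%.

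**Step 3: how often the condition is met.** 0.40 × 246 = 98.4, so about 98 patients are randomized at the look, about 49 of them to the intervention. Since 10% of 49 is 4.9, an observed rate above 10% means 5 or more refusals. With X ~ Binomial(49, p), P(X ≥ 5) is:

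- true refusal 30% (on plan): 0.9998
- true refusal 20% (better than plan): 0.98
- true refusal 10%: 0.55

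**Step 4: a rule anchored at 30%.** Required N varies with the inverse square of the difference, so N_new = 246 × (0.70 / observed uptake)². At 40% refusal, 246 × (0.70 / 0.60)² = 335. The smallest count above 30% is 15 of 49 (30.6% refusal, uptake 34/49 = 0.694), which gives 246 × (0.70 / 0.694)² ≈ 250.

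**The case against.** Four points can be made for the text as it stands.

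- **The rule is permissive.** Re-estimation may be considered; nothing is automatic. A recalculation on the plan's inputs at 20% or 30% refusal returns 186 or 244 patients, which would show that no increase is needed. The interim quantities are refusal and completion, not outcome comparisons, so no type I error problem is evident. This is right and limits the harm. It does not rescue a condition that is met almost regardless of what happens.
- **The 10% may mean an excess over 30%.** That is possible, but the sentence attaches the figure to the refusal rate itself. Read as 10 percentage points over, the threshold is 40%, where power is already about 67%. Read as a relative excess, it is 33%, with power about 77%. Rewording is needed under either reading.
- **Missing outcomes could justify acting below 30%.** The article gives no attrition figure. Taking 10%, 20% and 30% missing as an assumed range, power at 30% refusal is 76%, 71% and 65%, and it falls below 80% once refusal exceeds about 26%, 22% and 17%. This stands as a reason to judge refusal jointly with completion. It does not make 10% the expected rate, and even at 30% missing the crossing point lies above 10%.
- **A 30% threshold is noisy.** With true refusal exactly 30%, the chance of 15 or more refusals in 49 is 0.52. That is so, but the recalculation then asks for only a few more patients when the observed rate is just above 30% (about 250 at 15 of 49). The formula therefore matters as much as the threshold.

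Deferral to the statistical analysis plan is no answer. The article defers the handling of non-adherence, but it prints this threshold.

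**Conclusion.** The concern holds. The article fixes 30% as the expected refusal rate and then defines higher than expected as above 10%. Only the 30% figure reproduces the sample size (244 against 246). As written, the condition is met with probability 0.9998 when the trial is on plan and 0.98 when refusal is 20% and power is about 90%.

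The power figures rest on the plan's own simplifications: SD 21 in both arms, no effect in patients who decline, and complete four-week data. The probabilities assume about 49 intervention patients at the look. The contradiction itself depends on none of these. It should be corrected, because a printed decision threshold that conflicts with the design gives no usable guidance. Which figure the authors intended cannot be known from the article.

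**What to change.** Reconcile the two sections. Replace the 10% threshold with the planning value of 30%, and state how the new size is calculated once it is exceeded: N_new = 246 × (0.70 / observed uptake)², applied only upwards, so that 246 is the floor. If a margin of 10 percentage points over the expectation was meant, write above 40% and state that power at that point is about 67%. Because the same look also measures completion of the primary outcome, it would help to say how observed completion enters the recalculation.

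The cost is one number and one formula in the protocol and the analysis plan, with no change for patients or data collection. It should be settled before the look. Recruitment opened on 28 April 2025, and at the planned 164 patients a year, 98 are reached after 98 / 164 ≈ 0.6 years, or about seven months. If the look has already taken place, the sponsor should document which threshold was applied and what was decided.

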### Outcomes

The primary outcome is patient satisfaction with care, specifically focusing on the domain of affective behavior, measured four weeks after enrollment into PRESENT + . Satisfaction will be assessed using the European Organisation for Research and Treatment of Cancer (EORTC) Satisfaction with Cancer Care core questionnaire (PATSAT-C33) [32]. Patients will rate their experience on five-point Likert scales ranging from poor to excellent. The primary analysis will focus on the four-item subscale Affective Behavior. The PATSAT-C33 has been slightly adapted as participants will be asked to evaluate care provided by ‘healthcare providers in the hospital(s) in which they received oncological care’ instead of ‘nurses and radiotherapy technicians’.

Secondary outcomes will include patient-reported measures and overall survival:

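### The missing-data sensitivity analysis depends on a finding of MNAR that observed data cannot supply, and its only named method has undefined fill values

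*Protocol article*

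**What the plan says.** Everything on this point is in the last paragraph of the Statistical analysis section of the protocol article. It has three steps.

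- Missingness is first described: "The extent and patterns of missing data will be evaluated".
- The main handling follows: "If appropriate, multiple imputation methods will be used to address missing data under the assumption that data is missing at random (MAR").
- The robustness check comes last and is conditional: "If the primary outcome data is determined to be missing not at random (MNAR), sensitivity analyses using". The method it goes on to name is a pair of extreme-case analyses, best-worst and its reverse.

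The section does not say how MNAR would be determined, or which values stand for best and worst. No expected missing fraction appears there or in the Sample size section. The same section promises a separate SAP and says in general terms: "Secondary and sensitivity analyses will be specified to address alternative clinical questions and analytical scenarios". That sentence does not mention missing data.

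**The concern.** MAR and MNAR differ in whether non-response depends on the unseen score once the observed data are taken into account. Patterns in the observed data can argue against data being missing completely at random. They cannot show which of MAR and MNAR holds, because the information needed is exactly what is missing. A sensitivity analysis exists because MAR is untestable, so making it wait for a verdict on MAR reverses the logic.

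Two consequences follow. The team may see nothing it regards as evidence of MNAR and report the MAR result with no robustness check. Or someone may decide that the data are MNAR after seeing them, so that the check is run by a judgement made with the data in view. The outcome is satisfaction with care, and it is plausible that returning the questionnaire is related to the score it would have carried. A check that always runs is therefore worth having.

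The second issue is the method. If best and worst mean the ends of the scale, the check may span both signs at modest missingness, even when the planned effect is fully present. If they mean something milder, it may not. The text leaves this open.

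**Working it through.** **Inputs from the protocol article**

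- Sample size section: 246 patients; two-sided alpha 0.05; 80% power; 30% refusal; control mean and SD from a previous study, which "was 70.0 (SD = 21) among patients with metastatic solid tumors"; intervention-arm mean 0.7 × 80.8 + 0.3 × 70.0.
- Study design section: 1:1 allocation, so 123 per arm.
- Outcomes section: "Patients will rate their experience on five-point Likert scales ranging from poor to excellent", with four items in the primary subscale.

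**Assumptions, because the document gives no figure**

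- Missing fraction m per arm, equal in both arms: 5%, 10%, 20% (30% in the last step).
- A 0-100 score for the subscale. The Outcomes section states this transform for the quality-of-life scales but not for PATSAT-C33. It is inferred from the mean of 70.0 and SD of 21.
- Responders show the planned difference.

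**Step 1. Reproduce the plan's own figure.** 0.7 × 80.8 + 0.3 × 70.0 = 77.56, and 77.56 - 70.0 = 7.56, stated as 7.6. The detectable difference is (1.960 + 0.842) × 21 × √(2/123) = 7.50 (7.53 by the t-test). Power for 7.56 is 80.6% (80.3% by the t-test). The sample size reproduces and is not at issue.

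**Step 2. Bounds with fills of 0 and 100.** Best-worst gives 100 to missing intervention patients and 0 to missing controls; worst-best does the reverse. The two estimates are (1 - m) × 7.56 ± 100m, a width of 200m.

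| m per arm | Worst-best | Best-worst |
|---|---|---|
| 5% | 7.18 - 5 = 2.2 | 7.18 + 5 = 12.2 |
| 10% | 6.80 - 10 = -3.2 | 6.80 + 10 = 16.8 |
| 20% | 6.05 - 20 = -14.0 | 6.05 + 20 = 26.0 |

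The lower bound reaches zero when (1 - m) × 7.56 = 100m, that is m = 7.56/107.56 = 7.0%. The width passes the 7.6-point target at m = 7.6/200 = 3.8%.

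**Step 3. Bounds with milder fills.** Setting missing scores to the arm mean ± 1 SD, in opposite directions by arm, gives 7.56 ± 2 × 21 × m = 7.56 ± 42m.

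| m per arm | Lower | Upper |
|---|---|---|
| 5% | 5.5 | 9.7 |
| 10% | 3.4 | 11.8 |
| 20% | -0.8 | 16.0 |

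The sign changes at m = 7.56/42 = 18%. With the variance of the filled values included, the 95% interval for the lower scenario is 0.2 to 10.7 at 5% and -1.9 to 8.6 at 10%, so significance is lost between those two fractions.

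**Step 4. What a delta-adjusted analysis would show.** If missing intervention scores lie δ points below the MAR prediction and control scores are not shifted, the estimate is 7.56 - δm. For δ = 10 it is 6.56, 5.56 and 4.56 at 10%, 20% and 30% missing. Using the complete-case standard error 21 × √(2/(123(1 - m))), significance is lost at δ = (7.56 - 1.96 × SE)/m:

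- 10% missing: (7.56 - 5.53)/0.1 = about 20 points
- 20% missing: (7.56 - 5.87)/0.2 = about 8.5 points
- 30% missing: (7.56 - 6.27)/0.3 = about 4.3 points

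A reader can judge whether shifts of that size are credible.

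**The case against.** The strongest reply has four parts.

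**The magnitude is not in the document.** The fills, the 0-100 scale and the missing fractions are all assumed. A reader might infer that the best/worst bounds are simply too wide to inform. That holds only if the fills are the scale ends and missingness is not small. With ± 1 SD fills at 10% missing, both bounds stay above zero. This part of the objection stands.

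**Determined may mean judged.** It can be read as a view formed from reasons for non-return, not as a statistical test. A reader might infer that the condition can never be met and the check will never run. The text does not show that. It does show that the trigger is undefined and would be applied after the data are seen, which is enough for the point.

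**Other threats are mitigated or belong to the SAP.** A reader might infer that arm-related MNAR is the main threat to the primary result. No figure in the document shows high or differential non-return. The article also describes a reminder after one week, continued cohort follow-up of patients who refrain or withdraw from the trial, and an intermediate check of primary-outcome completion. A reader might also infer that scores would be imputed for patients who died before week 4. The text does not say so, and the handling of deaths is normally settled in the SAP.

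**The SAP may add analyses.** It may, and the article promises further sensitivity analyses. But the article itself fixes the MNAR condition and names the method. More analyses elsewhere would not make that condition sound.

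**Conclusion.** The stated rule is unsound: the only missing-data sensitivity analysis named in the article depends on a determination that evaluating observed missingness cannot deliver. The robustness check of the MAR imputation could be left out or triggered by judgement after the data are seen. This conclusion rests on the text alone and needs no numerical assumption.

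The size of the second issue does depend on assumptions. If the fills are the ends of a 0-100 scale and missingness is equal by arm, the planned effect no longer keeps its sign in the worst case from about 7% missing. With mean ± 1 SD fills, that happens at about 18%. Extreme-case bounds are a legitimate method, so naming them is not an error. The weakness is that they are the only method named and their fill values are undefined.

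**What to change.** In the Statistical analysis section, and in the SAP before data analysis:

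1. Delete the condition that the primary outcome first be found to be MNAR. State that the sensitivity analysis always accompanies the MAR analysis.
2. Make it a delta-adjusted (tipping-point) analysis around the MAR imputation. Shift imputed scores separately by arm over a range fixed in advance, and report the shift, or pair of shifts, at which the conclusion changes.
3. Keep best-worst and worst-best as an extreme bound, with the fill values written down.

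The cost is revised wording and a few extra model runs. No new data are needed. The article expects recruitment to end in the first quarter of 2027 and the SAP to be published before analysis, so the SAP can carry the change.

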### Trial status

Patient recruitment started on April 28, 2025 and is expected to conclude in the first quarter of 2027. Data collection (of the primary outcome) will conclude four weeks after enrollment of the last patient. Study results are expected to be available in 2027 and will be submitted for publication.

## Discussion

Timely referral of patients with cancer who receive radiotherapy for symptomatic bone metastases to specialist palliative care remains a significant challenge, especially in this heterogeneous and clinical complex patient population requiring comprehensive, multidisciplinary care [17,41,42]. Due to the often complex symptom burden, including symptoms like pain, treatment-related side-effects, skeletal complications such as pathological fractures, neurological symptoms including spinal cord compression, alongside emotional, social and spiritual distress, and loss of mobility and independence, patients may require specialist palliative care. However, the integration of specialist palliative care into oncological care is not standard. Referrals are typically reactive, only when situations are complex, hindered by several barriers for both clinicians and patients.

Effective strategies are needed to ensure that all patients who may benefit from specialist palliative care are given the option to meet with a palliative care consultant. In order to achieve such, they should be adequately informed and appropriately referred. One potential strategy is the systematic referral of all patients, which ensures that every patient is made aware of the potential benefits of specialist palliative care and can make an informed decision about engaging with these services, now, or at a later stage during their disease trajectory. This approach empowers patients and family caregivers and enables timely access to specialized palliative care for those in need. However, there is a risk of overtreatment as not all patients require specialist palliative care and for some patients, generalist palliative care provided by the general practitioner, nurse specialists or treating physician may be more appropriate. Given the often limited availability of palliative care resources (e.g., personnel and costs), it remains important to deliver the right care at the right time and in the right setting.

A strategy for preselecting patients for specialist palliative care referral could be to refer only those patients who meet predefined criteria. A Delphi study involving clinicians in oncology and/or palliative care examined the use of predefined criteria to trigger systematic referral versus physician-based referral. The study reached consensus supporting combined use of systematic and physician-based referral [43]. The expert panel emphasized that systematic referral facilitates more frequent and timely referrals. In a randomized trial by Groenvold et al., patients with advanced cancer were first screened for palliative care needs using the EORTC QLQ-C30 questionnaire before being referred to palliative care [44,45]. Of the 1,146 patients screened, 621 patients (54%) did not meet criteria for palliative care needs based on symptom burden and functional impairment. Additionally, 124 of 464 patients eligible for randomization (27%) declined participation [45]. Palliative care needs are unlikely to be fully captured by questionnaires alone and may become apparement during the consultation.

Our study provides insight into the physical, psychosocial, and spiritual characteristics and symptoms of patients who accepted a consultation with the PCCT, reasons for refraining from the consultation, and whether patients perceived it as valuable or not.It will also be assessed whether involvement of a specialist PCCT was necessary or whether generalist palliative care would have been appropriate for most patients. These findings may inform future clinical practice in defining referral criteria and optimizing the timing to identify patients most likely to benefit from specialist PCCT. Given the limited availability of PCCT resources, such evidence is essential for developing effective triage strategies.

This study according to the TwiCs design aims to provide real-world evidence on the effect of systematic referral of patients with bone metastases to specialist palliative care [24,26,46]. The recruitment process mirrors clinical practice, thereby enhancing the external validity and generalizability of the findings. First, the pragmatic nature of the trial offers valuable insights into the uptake of specialist palliative care in patients with bone metastases, including the uptake of the intervention and the identification of patients who require specialist palliative care. Second, as control patients are not informed about the study, potential bias due to disappointment upon being assigned to the control group is avoided [47]. This approach mitigates risks of contamination (i.e., patients actively seeking the intervention) and dilution of the estimated treatment effect, as well as reduces the likelihood that patients discontinue participation due to dissatisfaction or selectively reporting less favorable outcomes based on knowledge of not receiving the promising intervention (response bias). Previous research indicated that most patients had positive or neutral reactions to being part of the control group without notification [47]. Third, by comparing the intervention to usual care, that is not systematically offering a consultation with the hospital PCCT at referral for palliative radiotherapy, this study evaluates the effectiveness of the intervention within current clinical practices. In usual care, clinicians may refer patients for specialist palliative care when deemed appropriate or when patients express a desire for referral. However, it is not common in current clinical practice that patients are referred, and if referred, it is often late in the disease trajectory [48].

